## Summary

|                               |                                                                                                                                                                                                                                                                                                                                                                                                                                                                                                                                                                       |
|-------------------------------|-----------------------------------------------------------------------------------------------------------------------------------------------------------------------------------------------------------------------------------------------------------------------------------------------------------------------------------------------------------------------------------------------------------------------------------------------------------------------------------------------------------------------------------------------------------------------|
| Protocol title:        | Randomized controlled trial of the effects of graded support on symptoms of anxiety and depression using an Internet-based education program for anxiety and depression                                                                                                                                                                                                                                                                                                                                                                                               |
| Protocol version:      | 1.0                                                                                                                                                                                                                                                                                                                                                                                                                                                                                                                                                                   |
| Objectives:            | 
Primary objectives: To determine the benefits of different levels of support on the efficacy of an internet-delivered trans-diagnostic iCBT education program for anxiety and depression.
 
Secondary objective: To determine variables likely to facilitate completion rates, satisfaction, and acceptability to consumers.
 
The results will inform us about who is likely to benefit from a trans-diagnostic education protocol and how best to administer this program.
                                                           |
| Study design:          | 
A CONSORT-R compliant, registered RCT with 4 parallel groups (total sample size=350):
 
Group 1: Waitlist control (n=50). Receive access to the program once the other groups have completed the program (week 9).
 
Group 2: Self-guided (n=100). Receive immediate access to the program.
 
Group 3: Self-guided + automatic emails (n=100). Receive immediate access to the program.
 
Group 4: Self-guided + automatic emails + weekly telephone support (n=100). Receive immediate access to the program.
 |
| Planned sample size:   | 350                                                                                                                                                                                                                                                                                                                                                                                                                                                                                                                                                                   |
| Selection criteria:    | Australian adults aged 18-64 with elevated symptoms of depression and/or anxiety based on clinical measures.                                                                                                                                                                                                                                                                                                                                                                                                                                                          |
| Study procedure:       | Recruit and treat participants with elevated symptoms of depression and/or anxiety using a 5-lesson Internet-based education program. Three groups begin the program immediately, with graded levels of support (none vs. automatic emails vs. automatic emails + weekly phone calls). Their results are compared with a waitlist control condition.                                                                                                                                                                                                                  |
| Stat considerations:   | The design is powered to detect a between-groups effect size difference of 0.35 (alpha of 0.05, and power of 0.80) between Groups 2, 3, and 4. The design is also powered to detect a between-groups effect size difference of 0.55 between Group 1 and Groups 2, 3, and 4. Analyses will be conducted using intention-to-treat and completer models. Categorical data will be analysed via chi-squared tests and continuous data via parametric or equivalent non-parametric tests, including ANCOVAs and mixed linear models.                                       |
| Duration of the Study: | 23 months                                                                                                                                                                                                                                                                                                                                                                                                                                                                                                                                                             |

| TABLE OF CONTENTS                                                      | PAGE |
|------------------------------------------------------------------------|------|
| 1. BACKGROUND                                                          | 5    |
| 1.1 Disease Background                                                 | 5    |
| 1.2 Rationale for Performing the Study                                 | 5    |
| 2. STUDY OBJECTIVES                                                    |      |
| 2.1 Primary Objective                                                  | 6    |
| 2.2 Secondary Objective                                                | 7    |
| 3. STUDY DESIGN                                                        |      |

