- Participants may have full access to the program materials (Group 2: Self-Guided Group), full access + automatic emails (Group 3: Self-Guided + Automatic Emails Group), or full access + automatic emails + telephone support (Group 4: Weekly Support + Automatic Emails Group). The Waitlist Control Group (Group 1) will have access to the Self-Guided + Automatic Emails Group and will begin the program at week 9, once the education groups (Groups 2, 3, & 4) have completed.

**Outcome Measures:** We will measure changes in symptom level at the beginning of the 8 week program course of education, one week after the conclusion of education, at 3 month follow up, and at 12 month follow-up. The outcome measures will be the:

- Patient Health Questionnaire-9 Item (PHQ-9) [13]: Measures symptoms of depression.
- Generalized Anxiety Disorder-7 Item Scale (GAD-7) [14]: Measures symptoms of anxiety.
- Depression, Anxiety and Stress Scales-21 Item (DASS-21) [15]: Measures symptoms of anxiety, stress, and depression.
- The Panic Disorder Severity Rating Scale-Self Report [16]: Measures symptoms of panic disorder.
- The Social Phobia-12 [17]: Measures symptoms of social phobia.
- World Health Organisation Disability Assessment Schedule – 2nd Edition (WHODAS-II) [18]: Measures symptoms of disability.
- Kessler-10 Item (K-10) [19]: Measures symptoms of psychological distress.
- NEO-Five Factor Inventory – Neuroticism Subscale (NEO-FFI-NI) [20]: Measures personality features believed to underlie anxiety and depressive symptoms.

In addition, the GAD-7 and PHQ-9 will be administered at the beginning of each lesson to monitor anxiety and mood. We will also encourage feedback from participants at every stage of the project to determine how to improve the content and delivery of the program.

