## 4. PARTICIPANT SELECTION

### 4.1. INCLUSION CRITERIA

1. Elevated symptoms of depression or anxiety as indicated by: Total scores on at least one of the following measures: PHQ-9 > 9; GAD-7 > 7; Mini SPIN > 5 [21]; ANSQ > 1 [22]. Scores above these cut-offs indicate likelihood of meeting diagnostic criteria for at least one of: depression, generalized anxiety disorder, social phobia, panic disorder, respectively.
2. Self-identifying as having difficulties with either depression, social phobia, panic disorder, or generalized anxiety disorder. Note that meeting diagnostic criteria for a formal anxiety disorder or depression is NOT an inclusion criteria – instead, participants need to have elevated symptoms of anxiety or depression as indicated in (1), above.
3. No current participation in cognitive behavioural treatment.
4. No change in medications in the period 1 month prior to this study, and no change in medications during the study.
5. Access to the Internet and a printer.

6. 18 years to 64 years old.
7. Resident of Australia.
8. Prepared to provide name, phone number and address, and to provide the name and address of a local general practitioner
9. Prepared to provide written informed consent.

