  - b. Learn about the principles of CBT
2. *Lesson 2:*
  - a. Learn about the relationship between the way you think and feel
  - b. Begin monitoring and challenging unhelpful thinking patterns
3. *Lesson 3:*
  - a. Learn about physical symptoms of anxiety and depression and managing these with de-arousal and activation techniques
  - b. Assertiveness skills
4. *Lesson 4:*
  - a. Learn about behaviours (low activity and avoidance) that make anxiety and depression worse, and how to challenge those behaviours
5. *Lesson 5:*
  - a) Learn about problem solving, relapse prevention and staying well

On application, applicants will complete screening measures of anxiety and depression. Those with scores too high or too low (asymptomatic) will not be eligible. Eligible applicants will be telephoned by

the researchers, who will conduct diagnostic interviews via telephone. Applicants who meet diagnostic criteria for a primary disorder other than those targeted by this education protocol will not be eligible but will be informed about other options for education or treatment.

At the beginning of the education program all participants will complete the outcome measure questionnaires. The questionnaires being administered in this study are all valid and reliable clinical and research measures.

All participants will complete a second entire set of questionnaires at the post-education point (Primary Endpoint) and will also be telephoned by the researchers who will conduct the telephone interviews again. Participants in Groups 2, 3 and 4 will also be asked to complete a shorter set of questionnaires at 3 and 12 months follow-up. Participants in Group 1 (Waitlist control group) will begin the program immediately after the other groups have completed the education.

In addition, brief measures of anxiety and depression (the GAD-7 and PHQ-9) will be administered at the beginning of each lesson to monitor anxiety and mood. We will also encourage feedback from participants at every stage of the project to determine how to improve the content and delivery of the program.

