#### 5.7. RANDOMIZATION PROCEDURE

The website [www.random.org](http://www.random.org) will be used to determine a list of randomly generated numbers that correspond to a group. Such a list will be generated by an overseas colleague. Participants will be randomly allocated to one of the four groups after they complete the diagnostic interview.

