#### **8.2. ANALYSIS PLAN**

Analyses will be conducted using intention-to-treat and completer models. Categorical data will be analysed via chi-squared tests, and continuous data via parametric or equivalent non-parametric tests including ANCOVAs and mixed linear models.

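### Only chi-squared tests are named for categorical data; comparing interview diagnosis without its baseline value would usually cost power and blur the result

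*Protocol*

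**What the plan says.** Section 8.2 of the protocol treats the two kinds of data differently. Categorical data go to chi-squared tests, as in the Summary ("Categorical data will be analysed via chi-squared tests"). The same sentence of 8.2 then gives "continuous data via parametric or equivalent non-parametric tests including ANCOVAs and mixed linear models". No other categorical method is named. The analyses are to be intention-to-treat and completer, and no analysis set is restricted to people with a diagnosis at entry.

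On diagnosis itself:

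- **Entry.** Section 4.1, item 2, says that "meeting diagnostic criteria for a formal anxiety disorder or depression is NOT an inclusion criteria". Raised symptom scores and self-identification are enough, and 5.4 repeats this.
- **Baseline.** Section 5.7 says "Participants will be randomly allocated to one of the four groups after they complete the diagnostic interview". Section 5.4 names the instrument, a structured telephone interview.
- **Post-education.** Under 5.2, all participants complete the questionnaires at the Primary Endpoint and "will also be telephoned by the researchers who will conduct the telephone interviews again". The flow table in 5.1 shows the interview at that point in all four groups, and at 12 months in Groups 2–4.
- **Status.** Section 1.2 opens its list with "The outcome measures will be the" and then gives eight questionnaires. Diagnosis is not among them, nor is it in the hypotheses in 2.1.

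**The concern.** People without a diagnosis at entry will mostly have none at week 9, whichever arm they are in. Baseline diagnosis is therefore likely to predict week-9 diagnosis strongly. It is known before allocation, so it can safely be used as a stratification factor or covariate.

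The plan allows for this kind of baseline information in its continuous outcomes, through ANCOVA and mixed models, but names nothing comparable for categorical ones. Read with the intention-to-treat statement, the most natural reading is a table of week-9 diagnosis by arm in everyone randomised. Such a table has two weaknesses. The variation due to baseline diagnosis stays in the error, which costs power. And the diagnosis-free percentage mixes people who lost a diagnosis with people who had none to lose, so it is hard to interpret and the arm difference is diluted.

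**Working it through.** **Inputs**

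- 100 per active group, 50 in Group 1: sections 3.3 and 8.1.
- Alpha 0.05: section 8.1. Sidedness is not stated; two-sided is assumed.
- Share diagnosed at baseline, p: not given; assumed 50% to 95%.
- Still diagnosed at week 9 among those diagnosed at baseline: not given; assumed 60% v 40%.
- Diagnosed at week 9 among those not diagnosed at baseline: not given; assumed 5% in both arms.
- No dropout (assumed).

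The protocol states no power or rate for diagnosis or any other categorical outcome. Section 8.1 sizes the trial on standardised effect sizes, so there is no figure on this point to reproduce.

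**Step 1: pooled rates at p = 70%**

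- Arm A: 0.7 × 0.60 + 0.3 × 0.05 = 0.435
- Arm B: 0.7 × 0.40 + 0.3 × 0.05 = 0.295
- Difference: 0.140. A 20-point difference among the diagnosed becomes 14 points when everyone is pooled.

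**Step 2: power of the unstratified test**

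- SE under no difference: √(2 × 0.365 × 0.635 / 100) = 0.0681
- SE under the assumed difference: √((0.435 × 0.565 + 0.295 × 0.705) / 100) = 0.0674
- (0.140 − 1.96 × 0.0681) / 0.0674 = 0.097, so power is about 54%

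**Step 3: power when stratified by baseline diagnosis**

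The weighted difference is the same (0.7 × 0.20 + 0.3 × 0 = 0.140), but only within-stratum variation remains.

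- SE under no difference: √((0.7 × 2 × 0.5 × 0.5 + 0.3 × 2 × 0.05 × 0.95) / 100) = √0.003785 = 0.0615
- SE under the assumed difference: √((0.7 × (0.24 + 0.24) + 0.0285) / 100) = √0.003645 = 0.0604
- (0.140 − 1.96 × 0.0615) / 0.0604 = 0.322, so power is about 63%

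Simulation with 60,000 runs gives 54.0% and 62.5% for the same setting. The gain comes from the smaller standard error.

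**Step 4: other baseline shares, same assumed rates, by simulation**

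| Diagnosed at baseline | Unstratified | Stratified | Loss (points) |
|---|---|---|---|
| 50% | 36% | 45% | about 9 |
| 70% | 54% | 63% | about 9 |
| 80% | 64% | 70% | 5–6 |
| 90% | 74% | 76% | 2 |
| 95% | – | – | none |

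Type I error was near 5% for both tests.

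**Step 5: how far the answer moves with the assumptions**

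The assumed rates were varied over 60 v 40%, 70 v 50%, 70 v 45%, 80 v 55% and 80 v 50% among those diagnosed at baseline, and 2–20% among the rest. Gain from stratifying, 100 v 100, in points:

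| Diagnosed at baseline | Minimum | Median | Maximum |
|---|---|---|---|
| 50% | 2.8 | 13.1 | 27.4 |
| 70% | 2.7 | 9.0 | 16.3 |
| 80% | 1.3 | 5.4 | 9.7 |
| 90% | 0.0 | 2.0 | 4.2 |
| 95% | −0.7 | 0.6 | 2.0 |

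For Group 1 against one active group (50 v 100) the medians are 8.2 at 70%, 5.7 at 80% and 2.6 at 90%.

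**Step 6: reading the pooled percentage**

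Take p = 70%, true remission 50%, and 5% newly diagnosed. Diagnosis-free overall is 1 − (0.7 × 0.5 + 0.3 × 0.05) = 63.5%, against 50% among those who had a diagnosis to lose. People undiagnosed at baseline make up 0.3 × 0.95 / 0.635 = 45% of the diagnosis-free group. With remission of 30–50% and new diagnoses of 0–10%, that share is 44–59% at p = 70% and 31–46% at p = 80%.

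**Step 7: chance imbalance**

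At p = 70%, the difference in baseline diagnosis between two arms of 100 has a standard deviation of √(2 × 0.7 × 0.3 / 100) = 6.5 points. The unstratified test's standard error already allows for this. It is noise that stratification removes, not bias.

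**The case against.** The strongest case against the point is that the protocol never says this analysis will be done. Diagnosis is outside the outcome list and the hypotheses. The flow table schedules the interview without attaching an analysis to it. The clearly categorical result among the hypotheses is completion, which has no baseline value and for which a plain chi-squared test is suitable. The plan's wording is also broad: a Mantel-Haenszel test is a chi-squared test, and so is a test confined to people diagnosed at baseline. Such details are often settled in a statistical analysis plan, which is not shown here.

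Much of this stands, and it limits what can be claimed. A reader might infer that the plan counts never-diagnosed people as recovered. The document does not support that: it defines neither recovery nor remission and sets no denominator. A reader might also infer that diagnosis is the main categorical clinical result, or that the baseline interview goes unused. Neither is stated, and under 5.2 and 5.4 the interview decides eligibility, by excluding applicants whose primary disorder is not one the program targets.

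What does not stand is that the wording is therefore harmless. It names one family of tests for categorical data, reserves ANCOVA and mixed models for continuous data in the same sentence, and couples this with intention-to-treat. The obvious implementation leaves baseline out, although every participant has the interview before allocation and is due to have it again.

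The restricted test deserves a fair hearing. In the 50 v 100 simulation at p = 70% with the assumed rates above, it had 49.5% power, against 46.2% stratified and 39.7% unstratified. That ordering assumes no effect among the undiagnosed, and the test leaves out some randomised participants. It is a reasonable companion, but the plan should say which comparison is meant.

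**Conclusion.** The point holds as a conditional one. If interview diagnosis is compared by an unstratified chi-squared test in all randomised participants, the comparison is valid but usually less powerful than the data allow, and its diagnosis-free percentage is hard to interpret.

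The size depends on rates that the protocol does not give. Under the main assumptions the loss is about 9 points of power at 50–70% baseline diagnosis and fades to nothing at 95%. Across the wider set of scenarios at 100 v 100 it runs from roughly 0 to 27 points. A single unconditional figure, such as 6 to 10 points, is not supported. High baseline prevalence is plausible, since 4.1 says that scores above the entry cut-offs point to a likely diagnosis, and the loss would then be small.

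A reader might also conclude that the plain test is biased or that the primary comparison is weakened. Neither follows. Randomisation protects the test, and the primary hypothesis concerns symptoms. This is a worthwhile, low-cost improvement to a supportive analysis.

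**What to change.** In the Summary and section 8.2:

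- Analyse interview diagnosis at post-education and at 12 months with a Mantel-Haenszel chi-squared test stratified by baseline interview diagnosis, or with logistic regression on group with baseline diagnosis as a covariate.
- Report remission only among those diagnosed at baseline, so that the denominator is fixed in advance.
- Keep the plain chi-squared test for completion and descriptive tables.

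State that the stratifying value comes from the interview held before allocation (5.4 and 5.7), because the flow table in 5.1 lists a pre-education interview below the randomisation row.

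The cost is a sentence or two in each place. No new data, visits or participants are needed. The risk is negligible: the largest loss from stratifying in any 100 v 100 scenario was 0.7 points of power, at 95% baseline diagnosis.

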## 1. BACKGROUND

### 1.1. DISEASE BACKGROUND

Depression and anxiety are the most common mental disorders, frequently co-occur, and are associated with considerable distress and disability. However, both the 1997 and 2007 Australian National Surveys of Mental Health and Wellbeing reported that less than 40% of those with anxiety or depression sought treatment each year and of those, less than 50% receive evidence-based treatments [1-2].

### 1.2. RATIONALE FOR PERFORMING THE STUDY

The planned project is part of a larger research program exploring the potential of Internet-based education and treatment programs for anxiety and depression. Since 2007 we have conducted 20 RCTs of Internet cognitive behavioural therapy (iCBT) programs for people with anxiety disorders (generalized anxiety disorder, social phobia, or panic disorder) or depression. This research program has generated more than 30 publications, all RCTs have been approved or ratified by the UNSW and SVH HRECs, and all RCTs have resulted in clinical outcomes at least comparable to treatment outcomes we obtain from our face-to-face clinic (the Anxiety Disorder Clinic at St Vincent's Hospital, Sydney). Importantly, these results are also at least as good as those reported in recent meta-analyses of iCBT for depression and anxiety [3-4].

We have also recently completed 3 RCTs of Internet transdiagnostic treatment partly funded by an NHMRC Project Grant (#630560), again with good clinical outcomes and high levels of acceptability. Transdiagnostic programs treat anxiety and depression in the same program, and are designed to address the common issue of psychiatric co-morbidity, that is, patients having symptoms of more than one type of anxiety or depressive disorder [5]. Because anxiety disorders and anxiety and depression frequently co-occur, transdiagnostic programs offer practical advantages in terms of the delivery and receipt of education or treatment; that is, one program rather than several.

Our programs, while effective, have mostly been tested in trials that include guidance provided by a clinician or technician. Important questions are: **What types of support are required to achieve positive outcomes, and can adequate gains be obtained from a brief self-guided education program?** An effective self-guided trans-diagnostic iCBT program would offer multiple additional advantages: It would be highly cost-effective; scalable; would improve access to evidence-based education and treatments; and would teach consumers practical strategies for managing their own mental health. Until recently, self-guided Internet programs for anxiety or depression have been associated with small benefits [6-8]. More recent self-guided programs for depression [9] and panic disorder [10] indicate greater benefits are possible. Our own studies of self-guided programs to treat social phobia have demonstrated that the addition of regular automatic emails (providing encouragement and notifying when additional resources were available) doubled completion rates, and significantly improved clinical outcomes, and satisfaction rates [11-12], resulting in effect sizes of 1.0 on measures of social phobia. We have replicated this finding in social phobia, but note that this has not been replicated in other disorders.

This study will recruit 350 Australian adults (aged 18-64 years) with elevated symptoms of anxiety or depression. These participants will be given access to the "Wellbeing Program", a 5 lesson iCBT program they will be invited to complete over 8 weeks. This program has been carefully developed using evidence-based CBT techniques, parts have been tested in over

20 RCTs, and consultations have been conducted with more than 1000 consumers. This 5-lesson version has been successfully tested in a pilot study but not in an RCT.

**Program Content:** Components of this program include:

- 5 online lessons that include illustrated stories about adults who learn to manage symptoms of anxiety and depression
- Homework assignments
- Additional downloadable printed material describing techniques for managing other symptoms, including sleep difficulties, communication skills, and healthy lifestyle changes
- Participants may have full access to the program materials (Group 2: Self-Guided Group), full access + automatic emails (Group 3: Self-Guided + Automatic Emails Group), or full access + automatic emails + telephone support (Group 4: Weekly Support + Automatic Emails Group). The Waitlist Control Group (Group 1) will have access to the Self-Guided + Automatic Emails Group and will begin the program at week 9, once the education groups (Groups 2, 3, & 4) have completed.

**Outcome Measures:** We will measure changes in symptom level at the beginning of the 8 week program course of education, one week after the conclusion of education, at 3 month follow up, and at 12 month follow-up. The outcome measures will be the:

- Patient Health Questionnaire-9 Item (PHQ-9) [13]: Measures symptoms of depression.
- Generalized Anxiety Disorder-7 Item Scale (GAD-7) [14]: Measures symptoms of anxiety.
- Depression, Anxiety and Stress Scales-21 Item (DASS-21) [15]: Measures symptoms of anxiety, stress, and depression.
- The Panic Disorder Severity Rating Scale-Self Report [16]: Measures symptoms of panic disorder.
- The Social Phobia-12 [17]: Measures symptoms of social phobia.
- World Health Organisation Disability Assessment Schedule – 2nd Edition (WHODAS-II) [18]: Measures symptoms of disability.
- Kessler-10 Item (K-10) [19]: Measures symptoms of psychological distress.
- NEO-Five Factor Inventory – Neuroticism Subscale (NEO-FFI-NI) [20]: Measures personality features believed to underlie anxiety and depressive symptoms.

In addition, the GAD-7 and PHQ-9 will be administered at the beginning of each lesson to monitor anxiety and mood. We will also encourage feedback from participants at every stage of the project to determine how to improve the content and delivery of the program.

